### Procedure for unblinding if needed {17b}

We do not anticipate any requirement for unblinding, but if required, the principal investigator or the data manager will have access to group allocations and any unblinding will be reported.

## Data collection and management

### Plans for assessment and collection of outcomes {18a}

Data associated with this study will be collected in the standardized case report forms (CRF) for the outcome analysis, and a specific supervisor will be responsible for reviewing the integrity, accuracy, and consistency of the data. To ensure the accuracy of data entry, three investigators (two endodontists and 1 radiologist) will be responsible for entering the data independently and data query forms (DQF) will be resolved by tracing the source data.

A questionnaire to score the patient postoperative pain levels will be administered by two investigators in periods of 24, 48, and 72 h and 7 days after the completion of a root canal treatment. Questionnaires of patient satisfaction rate with regard to the treatment and the patient preference in relation to the frequency of clinical visits will also be performed. The secondary outcomes will be obtained from self-administered questionnaires completed immediately after the completion of a root canal. All the data will be registered in document clouds (in a specific Microsoft 365 OneDrive institutional account files), and only authorized personnel will have access. Data monitoring will be independent from the investigators and competing interests.

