### Objectives {7}

Our principal objective in this randomized, prospective, double-blinded, controlled clinical trial is to evaluate the effectiveness of endodontic treatments conducted in a single visit with the use of ultrasonic irrigant activation and in two visits with the use of ultrasonic irrigant activation and with and without the use of Ca(OH)2 dressing, in mandibular molars with asymptomatic apical periodontitis regarding periradicular repair during a period of 2 years of clinical, radiographic, and tomographic follow-up. Our secondary objectives are to analyze patients’ postoperative pain levels in periods of 24, 48, and 72 h and 7 days after the completion of a root canal; patient’s satisfaction rate with the treatment that will be performed; and patient’s preference regarding the frequency of clinical visit.

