#### Secondary outcome measures

##### Patient’s postoperative pain using a questionnaire

Patients will answer a questionnaire for the analysis of postoperative pain, through the analog pain scale, in an interval of 24h, 48h, and 72h and 7 days: (0) no pain, (1) mild, (2) moderate, (3) severe, and (4) intense (Fig. 2).

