## Assignment of interventions: blinding

### Who will be blinded {17a}

As a double-blinded trial, the patients and outcome evaluators will be blinded to the group assignment until the completion of the study. As dentists cannot be blinded to treatment allocation due to the notable differences in the treatment methods, they will not be allowed to discuss the type of intervention with either patients or outcome evaluators.

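### Postoperative pain is to be administered by two unidentified investigators who may know the arm, and a later sentence on secondary outcomes contradicts the pain schedule

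*Protocol article*

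**What the plan says.** The protocol article's section on assessment and collection of outcomes {18a} describes pain collection this way: "A questionnaire to score the patient postoperative pain levels will be administered by two investigators in periods of 24, 48, and 72 h", with a further assessment at 7 days. It does not say who the two investigators are.

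The next sentence concerns satisfaction and preference: "Questionnaires of patient satisfaction rate with regard to the treatment and the patient preference in relation to the frequency of clinical visits". Then follows a general rule: "The secondary outcomes will be obtained from self-administered questionnaires completed immediately after the completion of a root canal". That rule is not limited to any particular secondary outcome.

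Pain is a secondary outcome. The Objectives {7} read "Our secondary objectives are to analyze patients’ postoperative pain levels", and the outcome definition under Secondary outcome measures reads "Patients will answer a questionnaire for the analysis of postoperative pain, through the analog pain scale, in an interval of 24h, 48h, and 72h", again with 7 days. The scale runs from 0 to 4.

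Section {17a} on blinding states that patients and outcome evaluators will be blinded and that the dentists cannot be. Its safeguard for the dentists is that "they will not be allowed to discuss the type of intervention with either patients or outcome evaluators".

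**The concern.** A pain grade on a five-point scale is easily influenced by the person who asks for it. If the operator asks, knowing the arm and perhaps expecting one approach to do well, the grades of one arm can drift. The blinding section guards against operators talking to evaluators, but that does nothing if an operator is the one collecting the score. The protocol hands the images to separate readers and describes no such separation for pain.

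At stake is the between-arm comparison of pain, which the protocol tests by Kruskal-Wallis. The primary outcome, periapical healing, is not touched.

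The second problem is one of text. The same section gives pain one timing in its own sentence and, taken literally, another in the general sentence on secondary outcomes.

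**Working it through.** No figure in the protocol bears on this, so the check is to set the sections side by side.

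**Who are the two investigators?**
- Study setting {9}: the trial runs in the private offices of two co-investigators.
- Exclusion criteria: the interviews and clinical examination for diagnosis are done by the examiners who also treat.
- Outcomes {12}: two examiners responsible for the study do all clinical examination; imaging goes to two other endodontists and a radiologist.
- Retention {18b} and Data management {19}: the two investigators search for lost patients and clarify data queries.

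Together these point to the two treating site investigators. The protocol never says so outright.

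**Do they know the arm?**
- Concealment mechanism {16b}: only investigators open the envelope, at the moment of intervention.
- Implementation {16c}: study investigators have access to the randomization list.
- Blinding {17a}: treating dentists cannot be blinded.

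If the two investigators are the operators, they know the arm. If they are other study investigators, {16c} still opens the list to them. On neither reading does the text secure blinding of whoever administers the pain form.

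**When is pain recorded?** Six statements give 24, 48 and 72 h and 7 days: the Abstract, Objectives {7}, Trial design {8}, the outcome definition, the pain sentence in {18a} ("will be administered by two investigators in periods of 24, 48, and 72 h and 7 days after the completion") and the Discussion. One statement, the general sentence in {18a}, gives the moment of completion for the secondary outcomes without excepting pain. The count is six to one, and the one directly follows the sentence on satisfaction and preference.

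**How is it recorded?** The outcome definition has the patient answer the form ("Patients will answer a questionnaire for the analysis of postoperative pain, through the analog pain scale, in an interval of 24h, 48h"). Section {11c} plans texts and calls reminding patients to answer questionnaires. Administered by investigators could therefore mean handed out and prompted, or asked by interview. The text does not settle which. The firm conflict is in timing; mode is merely unclear.

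**Illustration only.** None of these inputs comes from the protocol except the 50 patients per arm, the five grades and the test. Assume the same pain distribution in all arms at one time point (50, 30, 12, 6 and 2% over grades 0 to 4). Lower the grade by one category, with a floor at 0, in a random fraction f of one arm, then apply Kruskal-Wallis at 5%. The simulated false-positive rate per time point is:

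| f in one arm | Rejection rate |
|---|---|
| 0% | about 5% |
| 10% | about 6% |
| 20% | about 8% |
| 30% | about 13% |
| 40% | about 20% |
| 50% | about 30% |

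If the same shift is applied to all three arms, the rate stays near 5% at every f. The harm thus depends on the shift differing between arms, which is what knowledge of the arm makes possible.

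**The case against.** The strongest reply is that the staff's identity is inferred. Section {18a} also uses the word investigators for two endodontists and a radiologist who enter data, so the two could be other people. Administering may mean no more than handing out a form that the patient fills in, and nothing says that a dentist grades pain by interview. The timeline table and the pain form are not visible in the text at hand and may settle timing and mode. All of this stands, and it is why the point is that the wording permits unblinded elicitation. It does not show that such elicitation is planned. The reply does not remove the gap, because study investigators in general have access to the list.

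Some stronger readings are tempting but not supported:
- A reader might infer that pain would be recorded before any postoperative pain could occur, so that the 24 h to 7 day endpoint vanishes. Six statements fix the schedule, and a 7-day score cannot be taken at the end of treatment. The general sentence is loose wording.
- A reader might infer that the two offices would follow different rules and so distort the comparison of arms. Nothing suggests this. Groups come from one random list, so a difference between offices would tend to affect all arms alike; that adds noise and does not create a spurious difference.
- A reader might treat pain as the main patient-reported endpoint. The protocol lists it first of three secondary outcomes and does not rank them.
- The simulated rates might be read as the trial's error rate. Their inputs are assumed, and nothing in the protocol supports any particular f.

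**Conclusion.** The concern holds in limited form. As written, a subjective secondary outcome can be elicited by staff who know the allocation, contrary to the protocol's own promise of blinded outcome evaluation. Separately, one sentence in {18a} contradicts the pain schedule and needs narrowing.

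The conclusion on blinding rests on reading the two investigators as the treating site investigators, which several sections support but none states; the open access to the randomization list is the fallback. The size of any bias cannot be derived from the document. Under the assumptions above it runs from negligible, when 10% of one arm is shifted, to serious, when half of it is. The change should be made because it is cheap and removes an avoidable route for bias, not because a given inflation has been shown.

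**What to change.** In {18a}:
1. State that patients complete the 0 to 4 pain form themselves at 24, 48 and 72 h and 7 days, prompted by the text messages and calls already planned in {11c}. Replace the wording that has two investigators administer it.
2. State that treating dentists, and anyone else who knows the allocation, do not elicit, record or transcribe pain scores.
3. Limit the sentence on self-administration at the end of treatment to satisfaction and preference.

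The cost is an edit to the protocol and a take-home form or message link, with no extra staff. The downside is possibly a few more missed entries than with someone asking in person, which the planned reminders should limit.

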### Plans to promote participant retention and complete follow-up {18b}

A patient will be considered as lost-to-follow-up if no contact can be made during 24 months, after an active search from the two investigators. Participants will receive no financial compensation but they will be given the root canal and the restorative treatments of the teeth.

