## Methods: participants, interventions, and outcomes

### Study setting {9}

The study will be conducted in the private offices of two of the co-investigators involved in the study ([name] and [name]), located in the cities of Itabuna (Bahia) and Goiânia (Goiás), Brazil, respectively. All investigators and examiners are specialists in Endodontics with more than 10 years of clinical experience. They will participate in this randomized clinical trial after receiving adequate training to obtain a comprehensive view of the principles and strategy of the 3 clinical approaches that will be used. A total of 150 adult patients, aged between 18 and 60 years old, who voluntarily seek endodontic treatment in the Brazilian Unified Health System in the cities of Itabuna, in the State of Bahia, and in Goiânia, in the State of Goiás, Brazil. After an assessment of eligibility and informed consent, patients will be randomly assigned to one of 3 clinical study groups. Patients who agree to participate in this study will sign an informed consent form.

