#### Exclusion criteria

Patients may not participate in the study if they are as follows: (1) teeth with extensive coronary destruction that makes direct restoration with composite resin unfeasible, (2) calcified teeth, (3) teeth with incomplete root formation, (4) teeth with persistent exudation, (5) teeth with anatomical complexities that prevent endodontic treatment in a single visit, (6) teeth recommended for endodontic retreatment, (7) teeth with advanced periodontal pocket, and (8) teeth in which foraminal patency is not obtained.

Patients who present a profile that fits to that described in the inclusion and exclusion criteria will then be referred for evaluation by other examiners ([name], [name], and [name], experts in Endodontics for more than 15 years), for confirmation of diagnosis and treatment planning, if necessary. Patients who do not fit the required profile will be forwarded to the health unit of origin. All the steps of interviews and clinical examination necessary to complete the diagnosis will be carried out by the examiners who will perform the treatment.

Patients with systemic diseases (diabetes, transplants, heart disease, liver failure, and kidney failure) and immunodepressed patients are prohibited during the trial as these conditions can affect the oral functions.

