### Outcomes {12}

All the steps of clinical examination will be carried out by the two examiners responsible for the study. Imaging evaluation will be done by other 2 specialists in Endodontics and 1 radiologist. All are with at least 15 years of experience.

Assessments will also be carried out at 6 (IOPAR), 12 (IOPAR), and 24 (CBCT) months for analysis of the tissue repair process. The therapeutic effect evaluation criteria are the following: (1) success: after RCT, the tooth should be asymptomatic, without fistula, without pain on percussion and palpation tests, without edema and in normal chewing function, radiographically in the process of periapical lesion regression from the first assessment (time point) at 06 months, and fully repaired after 2 years with confirmation through CBCT; and (2) failure: after RCT, the tooth is symptomatic, with symptoms of apical infection such as pain and fistula. The radiographic examination demonstrates the absence of decreased apical lesion or an enlarged apical lesion [22, 23].

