### Data management {19}

Data are entered anonymously. Data collection will be monitored by a clinical research assistant. When requested, the two investigators will clarify the data. Data management is under the responsibility of the University of Brasilia.

The Data Management Coordinating Center will oversee the intra-study data-sharing process, with the involvement of the Data Management Subcommittee. Only the principal investigator will be given access to all the data with a special password. Other project investigators will have direct access to their own site’s data sets and other sites’ data by request. To ensure confidentiality, data dispersed to project team members will be blinded to any identifying participant information.

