### Methods in analysis to handle protocol non-adherence and any statistical methods to handle missing data {20c}

Protocol violations after randomization will be listed in the clinical study report, tabulated by subject and recruitment site. We will perform intention-to-treat analyses with a “missing=failure” strategy to the management of missing data.

Sensitivity analyses will be performed for the missing data management: multiple imputation, available data, and maximum bias.

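### Tracing of non-attenders is given to investigators who know the allocation, and under the missing-equals-failure rule any gap in tracing between arms moves the primary success rate

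*Protocol article*

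**What the plan says.** Under the retention heading {18b}, the protocol article states: "A patient will be considered as lost-to-follow-up if no contact can be made during 24 months", and this is to be decided "after an active search from the two investigators". No number, type or timing of attempts is given there. The adherence section {11c} promises text and telephone reminders to all patients without saying who sends them.

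The article does not name the two searchers by function. Three places suggest who they are. Study setting {9}: "The study will be conducted in the private offices of two of the co-investigators involved in the study". Exclusion criteria: the interviews and diagnostic examination "will be carried out by the examiners who will perform the treatment". Outcomes {12}: "All the steps of clinical examination will be carried out by the two examiners responsible for the study".

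On knowledge of the arm, the blinding section {17a} says that "dentists cannot be blinded to treatment allocation due to the notable differences in the treatment methods". The concealment and implementation sections {16b, 16c} let investigators open the envelopes and limit access to the randomization list to them. Only patients and outcome evaluators are blinded.

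On missing outcomes, section {20c} says: "We will perform intention-to-treat analyses with a “missing=failure” strategy to the management of missing data". It adds sensitivity analyses by multiple imputation, available data and maximum bias. The main outcome analysis under {20a} instead fills missing data by last observation carried forward (LOCF).

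**The concern.** Success is settled by a CBCT at 24 months, so a patient must be brought back to be counted. If absence is scored as failure, being found is part of the outcome. The people deciding how hard to look know the arm and, because they also examine the patients, probably know who is doing well. Blinded image reading cannot protect against this, since the selection happens before any image exists. The stated safeguard for the unblinded dentists, not discussing treatment with patients or evaluators, does not reach tracing effort either.

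At stake is a difference in success rates, created or hidden, in a trial described as double-blinded. The discussion section itself names long follow-up as a difficulty.

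**Working it through.** The plan has no figure of its own for this mechanism. Its 20% effect size (Sample size details) serves only as a yardstick.

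**Inputs from the document.** 70 teeth per arm (Sequence generation {16a}); Kruskal-Wallis test at 5% on success rates (Main outcome analysis); radiolucency still visible in 52 to 84% of cases after the first year (Sample size details).

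**Assumptions.** True repair p = 80% in every arm; teeth independent; attendance unrelated to outcome; attendance either 90/85/85% or 95/85/85%. The document gives none of these attendance or repair rates.

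**Formula.** Let a be attendance and c the proportion of filled-in values that count as success. Scored success = p·a + c·(1 − a), so the shift between two arms = (p − c) × attendance gap.

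**Missing equals failure (c = 0).**
- One repaired tooth not found costs its arm 1/70 = 1.4 points.
- Attendance 90/85/85%: 0.8 × 0.90 = 72% against 0.8 × 0.85 = 68%, a shift of 4 points.
- Attendance 95/85/85%: 0.8 × 0.95 = 76% against 68%, a shift of 8 points, which is 8/20 = 40% of the 20% effect if that means percentage points.
- Simulated rejection rates of the three-group test: 4.9% with equal attendance, about 7.6% at 90/85/85%, about 17% at 95/85/85%.

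**LOCF.** If a carried one-year reading must show full repair, the document's range gives c between 100 − 84 = 16% and 100 − 52 = 48%. I ran c from 16% to 50%.
- 95/85/85%, c = 16%: 0.8 × 0.95 + 0.16 × 0.05 = 76.8% against 0.8 × 0.85 + 0.16 × 0.15 = 70.4%, a shift of 6.4 points and about 13% false positives.
- 95/85/85%, c = 50%: 78.5% against 75.5%, a shift of 3.0 points and about 7%.
- 90/85/85%: about 5% to 7% over the same range of c.
- The shift vanishes at c = 80% and reverses above it, so even its direction depends on how carried readings are judged.

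**Available data.** With attendance unrelated to outcome, all arms show 80% among teeth seen, and the simulated rejection rate is about 4.9% in both scenarios.

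**Search that depends on arm and prognosis.** Suppose one arm finds 95% of its repaired teeth and 85% of its unrepaired ones, while the others find 85% of both. Under missing equals failure the arms again score 76% and 68%. The available-data analysis now gives 0.76/(0.76 + 0.2 × 0.85) = 0.76/0.93 = 81.7% against 80%, so 1.7 points of false difference remain.

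**The case against.** The strongest reply has four parts.

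- **The rule is not settled.** A reader might infer that every tooth not found is scored a failure. The document does not support that as it stands: {20c} says so, but the main outcome section prescribes LOCF, under which a tooth with a 6- or 12-month reading keeps it. This stands, and it reduces the size. It does not remove the route as long as carried readings succeed less often than teeth seen at 24 months.
- **The planned sensitivity analyses already help.** A reader might infer that they do nothing. In fact the available-data analysis removes the whole shift when only attendance differs, and maximum bias would show fragility. This largely stands. What they cannot undo is search that follows both arm and unrecorded prognosis, although the residual in the example above is small.
- **Identity and effort are not stated.** That the searchers are the treating dentists is inferred from three sections, and nothing suggests that they would favour an arm. Reminders and search are described without distinction by arm. This stands: the attendance gaps are assumptions. The inference matters less than it seems, because investigators generally have access to the list.
- **Contact schedules and logs are operational detail** that an article may leave to the full protocol. This is fair, and their absence is not the point. The point is that the procedure the article does state gives the task to people who know the arm.

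**Conclusion.** The point holds in limited form. The protocol assigns tracing to investigators who know the allocation and, on the most natural reading, treat the patients. Under the rule in {20c}, unequal tracing shifts the success rate by about the success rate times the attendance gap: 8 points and about 17% false positives for a 10-point gap, given an assumed 80% repair and 70 independent teeth per arm. Under LOCF the same gap gives about 7% to 13%. Clustering of teeth within patients (210 teeth in 150 patients) is ignored in these figures.

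A reader might go further and conclude that the primary result will be biased. The document does not support that. It shows an open route, not unequal effort, and a planned analysis would expose the simplest form. This is a worthwhile, inexpensive improvement rather than a defect that invalidates the design.

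**What to change.** In {18b}, assign recall and tracing at 6, 12 and 24 months to existing staff without access to the allocation. The clinical research assistant mentioned under Data management {19} ("Data collection will be monitored by a clinical research assistant") and under Adverse event reporting {22} is one candidate. State that every patient receives the same fixed set of contact attempts, that attempts are logged, and that attendance will be reported by arm at each time point. Because the document does not say that the assistant is blinded, and {27} gives assistants the final dataset, state also that the allocation is withheld from whoever does the tracing until follow-up closes.

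Separately, reconcile the main outcome analysis with {20c}, so that one missing-data rule governs the primary comparison and the other, if kept, is labelled a sensitivity analysis.

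The cost is a few lines of protocol text and some extra work for the assistant. Recall must be kept apart from the monitoring role, since {18a} wants data monitoring independent of the investigators. Treatment, sample size and outcome definition are unaffected.
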